## Abstract

**Background:**

The criteria applied for diagnosis of left atrial (LA) abnormality using electrocardiogram (ECG) have high specificity but low sensitivity. In fact, some authors have suggested classifying P‐wave anomalies associated with LA abnormality and interatrial block as “atrial abnormalities.” The most widely known ECG criteria for LA abnormality include P‐wave duration, morphology and voltage of P wave in inferior leads, presence of P‐wave terminal force in V_1_ (PtfV_1_), and P‐wave axis and area. PtfV_1_ has also been reported to vary according to misplacement of the V_1_ and V_2_ electrodes.

**Methods:**

The objective of this observational cohort study is to determine the degree of correlation between ECG criteria for LA abnormality and left atrium volume and functionality, as determined by speckle tracking echocardiography. The study also aims to investigate the correlation between these echocardiographic parameters and PtfV_1_ value by placing the V_1_ and V_2_ electrodes in the second, third, and fourth intercostal spaces.

**Results and Conclusions:**

Our results could help to clarify whether the decrease in left atrial deformity, which is currently considered a surrogate target of fibrosis, correlates better with ECG criteria for LA abnormality than atrial volumes.

## INTRODUCTION

1

The criteria applied for diagnosis of left atrial (LA) abnormality using electrocardiogram (ECG) are based on various parameters including P‐wave duration ≥ 120 ms, the classic Morris index (increase in P‐wave terminal force in V_1_ [PtfV_1_], with terminal negativity of P wave in V_1_ < −0.1 mV and duration >0.04 s) (Morris, Estes, Whalen, & Thompson, 1964), P‐wave morphology in inferior leads, P voltage in lead I, P‐wave area/axis, and P‐wave score(Alexander et al., 2019). These criteria have high specificity (85%–90%) but low sensitivity (Josephson, Kastor, & Morganroth, 1977; Tsao et al., 2008; Bayes de Luna, 2012) and can also be used for diagnosis of interatrial block (IAB). Therefore, a consensus statement of the American Heart Association suggests including these P‐wave changes, whether due to LA abnormality or IAB, as "P‐wave abnormalities" (Hancock et al., 2009). Furthermore, young athletes might have LA abnormality with P‐wave duration < 120 ms (Hock et al., 2019). The Morris index (Morris et al., 1964), which is the only criterion with acceptable sensitivity, was recently shown to be unreliable (Sajeev et al., 2019). Furthermore, the negativity of the P wave increases (Rasmussen et al., 2019) if the V_1_ electrode is placed in the second intercostal space. Some authors have suggested that this V_1_ pattern represents no more than an interatrial conduction defect and may not necessarily indicate LA abnormality (Josephson et al., 1977).

The main aim of our observational study is to compare the association between P‐wave criteria in patients with LA abnormality on transthoracic echocardiography (TTE). As secondary objectives, we aim to study the association between P‐wave criteria in patients with left atrium (LA) functional abnormalities on speckle tracking echocardiography (STE). In addition, we will analyze the correlation between these echocardiographic parameters and PtfV_1_ value by placing the V_1_ and V_2_ electrodes in the second, third, and fourth intercostal spaces.

## METHODS

2

### Design and study population

2.1

We will perform a prospective observational cohort study in the Echocardiography and Non‐invasive Cardiology Laboratory of the Hospital Universitario de Canarias. The study population will comprise patients referred for TTE (Figure 1).

**Figure 1 anec12770-fig-0001:**
[figure not shown]
Study design. A‐IAB, advanced interatrial block; PtfV1, P terminal force V1

### Inclusion criteria

2.2

Age ≥ 60 years.Signed informed consent.Optimal‐quality ECG and echocardiography images.

### Exclusion criteria

2.3

Poor transthoracic window.Atrial fibrillation (all types).Previous arrhythmias (atrial and ventricular).Absence of measurable P waves.Cardiac devices.Chest abnormalities (including pectus excavatum and straight back syndrome).Chronic obstructive pulmonary disease.

**Figure 2 anec12770-fig-0002:**
[figure not shown]
V1 lead of a healthy patient with normal left atrial size for echocardiography, with the V1 electrode located in the correct place: fourth intercostal space (4), third intercostal space (3), and second intercostal space (2). Note how a normal P wave becomes progressively negative as the V1 electrode is located upward

ECG parameters for assessment of LA abnormality:
P‐wave duration (<120 ms, 120–140 ms, >140 ms)P‐wave morphology in the inferior leads (nonbiphasic or biphasic)Presence of PtfV_1_
P voltage in lead I (>0.20 mV, 0.10–0.20 mV, <0.10 mV)P‐wave area and axisP‐wave MVP scoreLength of the P wave in lead II > 120 msLeft deviation of the middle axis of the P wave between −30 and −45º.

The ECG criteria for diagnosing RA abnormality are as follows:
P‐wave amplitude in lead II > 2.5 mm.Upward deflection of the P wave in lead V1 > 1.5 mm in amplitude.Increase of the area under the initial positive part of the P wave in V1 > 0.06 mm‐s.Right deviation of the middle axis of the P wave greater than +75º.

### Echocardiography studies

2.5

Echocardiography studies will be stored digitally and will be analyzed by 2 experienced operators ([name] and [name]), who will be blinded to the clinical ECG data. The operators will use a commercial system (iE33 xMATRIX, Koninklijke Philips NV) with a 2–4 MHz multifrequency transducer. Three consecutive beats will be recorded in a cineloop format during apnea. The analysis will be performed using an echocardiographic analysis system (Xcelera R2, Philips). LA and left ventricular (LV) measurements and LV ejection fraction and Doppler variables will be measured to quantify LV diastolic function according to standard echocardiographic methods (Nishimura & Tajik, 1997) (Table 1). The maximal LA volume (LAV max) will be traced in both the apical 4‐ and 2‐chamber views in the “frame” prior to mitral valve opening using the biplane disk summation algorithm to calculate its volume, adjusted for body surface area and considering an LAmax > 34 ml/m^2^ as increased (Lang et al., 2015). The size of the RA will be quantified using the apical four‐chamber view, and the volume will be determined using the disk summation technique in 2D mode (Lang, et al., 2015).

**Table 1 anec12770-tbl-0001:** Doppler echocardiography with atrial strain variables

LAmin, BS (ml/m^2^)
LAmax, BS (ml/m^2^)
LAVpre, BS (ml/m^2^)
Anteroposterior diameter measurement of left atrium in long axis parasternal in 2D, mm
LAEF, %
LAEF passive, %
LAEF active, %
LASr, %
LAScd, %
LASct, %
pLASRr, 1/s
pLASRcd, 1/s
pLASRct, 1/s
Pulsed mitral Doppler: E wave, cm/sec
Pulsed mitral Doppler: A wave, cm/sec
E/A ratio
E‐wave deceleration time, msec
A‐wave duration, msec
Pulsed Doppler pulmonary vein PVs, cm/sec
Pulsed Doppler pulmonary vein PVd, cm/sec
S/D ratio
Mitral annular tissue Doppler: e´ septal, cm/sec
Mitral annular tissue Doppler: a´, septal, cm/sec
Mitral annular tissue Doppler: s´, septal, cm/sec
Mitral annular tissue Doppler: e´, lateral, cm/sec
Mitral annular tissue Doppler: a´, lateral, cm/sec
Mitral annular tissue Doppler: s´, lateral, cm/sec
E/e´ ratio
Vp, cm/sec
E mitral/Vp ratio.
LVED dimension, mm
LVES dimension, mm
LVED volume index, ml/m^2^
LVES volume index, ml/m^2^
Relative wall thickness
Left ventricular mass index, g/m^2^
Left ventricular ejection fraction, biplane (%)
RA volume (ml/m^2^)
RASr, %
RAScd, %
RASct, %
pRASRr, 1/s
pRASRcd, 1/s
pRASRct, 1/s

Abbreviations: BS, body surface; LAEF, total left atrial emptying fraction; LAmax, maximum volume of left atrium; LAmin, minimum volume of left atrium; LAScd, left atrial strain during conduit phase; LASct, left atrial strain during contraction phase; LASr, left atrial strain during reservoir phase; LAVpre, left atrium volume at the beginning of the P wave of the ECG; LVED, left ventricular end‐diastolic; LVES, left ventricular end‐systolic; pLASRcd, left atrial peak strain rate during conduct phase; pLASRct, left atrial peak strain rate during contraction phase; pLASRr, left atrial peak strain rate during reservoir phase; pRASRcd, (negative) peak strain rate during conduit phase; pRASRct, (negative) peak strain rate during contraction phase; pRASRr, (positive) peak strain rate during reservoir phase; PVd, pulsed Doppler pulmonary vein, diastole pulmonary vein; PVs, pulsed Doppler pulmonary vein, systole pulmonary vein; RA, right atrial; RAScd, strain during conduit phase; RASct, strain during contraction phase; RASr, strain during reservoir phase; Vp, M mode color, left intraventricular propagation velocity.

For the STE of the LA, standard 2D images from apical 4‐ and 2‐chamber views will be acquired, with a narrow sector angle (30°–60°) and a frame rate of 60–90 frames per second (Badano et al., 2018). The LA endocardial border will be traced manually in both 4‐ and 2‐chamber views by marking 2 points at both ends of the mitral annulus and a third at the ceiling of the LA in end systole. The surface epicardial tracing is automatically generated by the system and can be adjusted manually by the operator in cases of tracking failure. Any segments that subsequently fail to track will be excluded. The LA myocardium will be divided into 12 segments of interest. For analysis, a longitudinal strain and strain rate (SR) will be measured automatically “offline” (Yasuda et al., 2015) using QLAB Advanced Tissue Motion Quantification (Philips) Release 8.1 equipped with STE analysis software. Global longitudinal strain and SR will be the average of the 12 values obtained for each LA segment (Table 1). Zero strain reference will be set at LV end diastole or when the LA speckle tracking is triggered on QRS onset (Badano et al., 2018)^,^(Olsen et al., 2016). The periods of the cardiac cycle will be determined after obtaining the LA longitudinal strain/SR and aligning them with the pulsed Doppler spectrum of the LV inflow and outflow tracts, starting at QRS onset (Badano et al., 2018)^,^(Olsen et al., 2016). RA deformation will be assessed in the apical four‐chamber view in 2D by starting the tracing at the endocardial border of the RA in the tricuspid annulus and continuing along the lateral wall of the RA, roof of the RA, and septal wall of the RA, before finishing at the opposite border of the tricuspid annulus. The apical four‐chamber view will be optimized by avoiding RA foreshortening, thus enabling—as with the LA—the volumes, strain, and strain rate of the RA to be determined (Badano et al., 2018).

### Other variables

2.6

Sociodemographic variables, presence of comorbidities, pharmacological treatments, and indications for echocardiography will be recorded (Table 2).

**Table 2 anec12770-tbl-0002:** Demographic variables and indications for echocardiography study

Demographic variables
Age
Sex
Height, cm
Weight, kg
BMI, kg/m^2^
BSA, m^2^
Diabetes mellitus
Smoking
Hypertension
Hyperlipidemia
TIA or previous stroke
Previous diagnosis of heart failure
Known coronary artery disease
Obstructive sleep apnea
CHADS_2_ score
CHA2DS₂‐VASc score
ACE inhibitors/ARBs
Beta blockers
Anticoagulants or NOACs
Antiplatelet agents
Antiarrhythmic agents
Indications for echocardiography study
Chest pain
Coronary artery disease
Valvulopathy
Cardiomyopathy
LVEF calculation
Dyspnea
Murmur
Syncope
Hypertension
Rule out structural heart disease
Pulmonary hypertension
Aortic aneurysm

Abbreviations: ACE, angiotensin‐converting enzyme; ARBs, angiotensin II receptor blockers; BMI, body mass index; BSA, body surface area; LVEF, left ventricular ejection fraction; NOACs, new oral anticoagulant agents; TIA, transitory ischemic attack.

### Sample size calculation

2.7

Previous data suggested that 92% of patients with LA abnormality might have a positive Morris index (Morris et al., 1964). We estimate that 79 patients with a positive Morris index are required to determine this rate with a confidence level of 95% and precision error of 6%.

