### Statistical analysis

2.8

Continuous variables will be compared using the *t* test or the Mann–Whitney test. Categorical variables will be compared using the chi‐square test. Based on the volume of LAV max by echocardiography, 2 groups will be established, as follows: increased volume and normal volume. Correlations between ECG and TTE STE variables will be obtained using the Spearman rank test and the intraclass correlation coefficient. We will use the logistic regression model adjusted for potential confounders, including variables that are significant in the univariate model. The ability of the multivariate logistic model to correlate with the LAV max group will be verified using receiver operating characteristic (ROC) curves. The overall accuracy, sensitivity, specificity, and positive and negative predictive values for the optimal cutoff will be calculated using the Youden index. Intra‐ and interobserver variability will be assessed using Bland–Altman analysis. All statistical analyses will be performed using IBM SPSS Statistics for Windows, Version 23 (IBM Corp., Armonk, NY, USA).

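### Section 2.7 attaches the 79 patients to the wrong group: a 92% rate among patients with LA abnormality needs 79 patients with LA abnormality, not 79 with a positive Morris index

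*Protocol article*

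**What the plan says.** Section 2.7 (Sample size calculation) has two sentences. The first gives the planning rate, from previous data: "92% of patients with LA abnormality might have a positive Morris index". The second gives the number: "We estimate that 79 patients with a positive Morris index are required to determine this rate". The target it sets is 6% precision at 95% confidence.

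Three other places bear on which patients are counted:

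- Section 2.1 defines who enters: "The study population will comprise patients referred for TTE". The inclusion and exclusion criteria in sections 2.2 and 2.3 do not mention the Morris index.
- Section 2.5 treats an indexed maximal LA volume above 34 ml/m² as increased. Section 2.8 builds the comparison on it: "Based on the volume of LAV max by echocardiography, 2 groups will be established, as follows: increased volume and normal volume".
- Section 2.8 also plans accuracy measures: "The overall accuracy, sensitivity, specificity, and positive and negative predictive values for the optimal cutoff will be calculated using the Youden index".

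The article gives no total enrolment and no expected prevalence of LA abnormality. The 79 is its only planning number.

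**The concern.** The two sentences of section 2.7 describe different denominators. The rate is P(Morris positive | LA abnormality), so it is estimated in patients with LA abnormality. Patients with a positive Morris index are something else: those of them who have LA abnormality form the numerator of that rate, and the rest are false positives who do not enter it at all. Morris-positive patients are the denominator of the positive predictive value, which section 2.7 does not name as its target.

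What is at stake is the precision claim. The half-width of a confidence interval for the 92% rate depends on how many patients with LA abnormality are enrolled. Counting Morris-positive patients fixes that number only indirectly, through a prevalence that the article does not state and a specificity that it gives only for the ECG criteria as a group.

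**Working it through.** **Inputs.** From section 2.7: p = 0.92, confidence 95% (read as two-sided, z = 1.96), precision 6% (read as an absolute half-width d = 0.06). From the Introduction: specificity 0.85 to 0.90, stated for the ECG criteria as a set and not for the Morris index alone. Prevalence of LA abnormality among the referrals: not in the document. I assume 20% to 60% and show the range.

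**Step 1: reproduce the 79.** The usual precision formula for one proportion is n = z² p(1 − p) / d².

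n = 1.96² × 0.92 × 0.08 / 0.06² = 0.28274 / 0.0036 = 78.54, rounded up to 79.

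The match is exact. Other readings do not give 79: a one-sided 95% level gives 56, and taking 6% as the full width (d = 0.03) gives 315. In this formula n is the denominator of the 92% proportion, so 79 is a number of patients with LA abnormality. With 79 of them, the half-width is 1.96 × √(0.92 × 0.08 / 79) = 0.0598, as the plan intends.

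**Step 2: what 79 Morris-positive patients provide.** In a cohort enrolled without regard to the Morris result:

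- P(Morris positive) = 0.92 × prev + (1 − spec) × (1 − prev)
- total N at which 79 Morris-positive patients are expected = 79 / P(Morris positive)
- expected patients with LA abnormality = N × prev
- half-width for the 92% rate = 1.96 × √(0.92 × 0.08 / number with LA abnormality)

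| Assumed prevalence | Specificity | P(Morris positive) | Total N | With LA abnormality | Half-width (points) |
|---|---|---|---|---|---|
| 20% | 0.85 | 0.304 | 259.9 | 52.0 | 7.4 |
| 20% | 0.90 | 0.264 | 299.2 | 59.8 | 6.9 |
| 30% | 0.85 | 0.381 | 207.3 | 62.2 | 6.7 |
| 30% | 0.90 | 0.346 | 228.3 | 68.5 | 6.4 |
| 40% | 0.85 | 0.458 | 172.5 | 69.0 | 6.4 |
| 40% | 0.90 | 0.428 | 184.6 | 73.8 | 6.2 |
| 50% | 0.85 | 0.535 | 147.7 | 73.8 | 6.2 |
| 50% | 0.90 | 0.510 | 154.9 | 77.5 | 6.0 |
| 60% | 0.85 | 0.612 | 129.1 | 77.5 | 6.0 |
| 60% | 0.90 | 0.592 | 133.4 | 80.1 | 5.9 |

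The two counts coincide only when false positives equal false negatives, that is when (1 − spec)(1 − prev) = 0.08 × prev. This happens at a prevalence of 0.10 / 0.18 = 56% for specificity 0.90, and 0.15 / 0.23 = 65% for specificity 0.85. Below that, 79 Morris-positive patients bring fewer than 79 patients with LA abnormality.

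**Step 3: the favourable limit.** If all 79 Morris-positive patients had LA abnormality, the expected number with LA abnormality would be 79 / 0.92 = 85.9, about 86, and the half-width 1.96 × √(0.0736 / 85.87) = 0.0574, or 5.7 points.

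**Step 4: totals if the 79 are counted correctly.** Total = 79 / prevalence, rounded up: 395 at 20%, 264 at 30%, 198 at 40%, 158 at 50%, 132 at 60%.

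**The case against.** The best defence is that the second sentence of section 2.7 carries on from the first, so that the 79 are Morris-positive patients among those with LA abnormality. About 86 patients with LA abnormality would then be implied, and the 5.7-point half-width meets the target. This stands as a possible intention, and it is why one cannot say that the 6% is certainly missed. But the text does not say it, and the formula gives 79 as the denominator, not as the positives within a larger one. With specificity below 100%, some Morris-positive referrals will have normal LA volume.

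A second defence is that the loss is small and rests on assumption. This also stands. The worst case shown is 7.4 points against 6.0, at an assumed prevalence of 20%; at 50% or more the loss is close to nil. The group comparisons, correlations, regression and ROC analysis in section 2.8 do not use this denominator.

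A third is that a condensed article may leave total enrolment to the full protocol. That is fair: the missing total is not the fault here. The fault is that the stated number is tied to a group that does not match the stated rate, and nothing elsewhere in the article corrects it.

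A reader might infer more from the sentence than it supports. One inference is that only Morris-positive patients are recruited, so that sensitivity would be 100% by construction. Sections 2.1 to 2.3 rule this out, since referrals enter without selection on the Morris index. Section 2.8 also forms a normal-volume group and plans specificity and negative predictive value. Another inference is that recruitment stops at the 79th Morris-positive patient. No such rule is stated; the only limit on inclusion is the calendar window in section 2.10.

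**Conclusion.** The point holds as a denominator error. Section 2.7 names patients with a positive Morris index where its own rate and formula require patients with LA abnormality. It should not be read as an arithmetic error, because 79 reproduces exactly.

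The consequence is that the stated precision is not secured. Under 92% sensitivity, 85–90% specificity and an assumed prevalence of 20–50%, the half-width is about 7.4 to 6.0 points, a loss of at most about 1.4 points; under the most favourable reading it is 5.7 points. These sizes depend on a prevalence that the article does not give and on a specificity that it does not state for the Morris index itself. The mismatch between rate and group depends on neither. I rate it as moderate: the study's only planning figure is misstated, but the likely effect on precision is limited and the remedy is simple.

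**What to change.** Reword the second sentence of section 2.7 along these lines: *79 patients with LA abnormality (LAmax > 34 ml/m²) are required to estimate the proportion with a positive Morris index with 95% confidence and 6% precision.* Say that they are counted among echocardiography referrals enrolled whatever their Morris result, which is how section 2.1 already describes the population.

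It would help to add the total that this implies, with the prevalence stated as an assumption: about 158 at 50%, 198 at 40%, 264 at 30%.

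The cost is one reworded paragraph. The figure of 79, the eligibility criteria and the planned analyses stay as they are. Depending on the prevalence chosen, the implied total may differ from what the investigators had in mind, and it should be checked against the inclusion window in section 2.10.

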### Statistical analysis

2.8

Continuous variables will be compared using the *t* test or the Mann–Whitney test. Categorical variables will be compared using the chi‐square test. Based on the volume of LAV max by echocardiography, 2 groups will be established, as follows: increased volume and normal volume. Correlations between ECG and TTE STE variables will be obtained using the Spearman rank test and the intraclass correlation coefficient. We will use the logistic regression model adjusted for potential confounders, including variables that are significant in the univariate model. The ability of the multivariate logistic model to correlate with the LAV max group will be verified using receiver operating characteristic (ROC) curves. The overall accuracy, sensitivity, specificity, and positive and negative predictive values for the optimal cutoff will be calculated using the Youden index. Intra‐ and interobserver variability will be assessed using Bland–Altman analysis. All statistical analyses will be performed using IBM SPSS Statistics for Windows, Version 23 (IBM Corp., Armonk, NY, USA).

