## CONCLUSION

3

Our prospective observational study will help to define ECG criteria for LA and RA abnormality and to distinguish IAB from LA abnormality.

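### The only ROC analysis described in section 2.8 is for a confounder-adjusted logistic model, so it does not isolate the diagnostic performance of the ECG criteria

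*Protocol article*

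**What the plan says.** Section 2.8 (Statistical analysis) splits patients into increased and normal LAV max. Section 2.5 sets the threshold: "considering an LAmax > 34 ml/m^2^ as increased". Three consecutive steps in section 2.8 then matter here:

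- The model: "We will use the logistic regression model adjusted for potential confounders, including variables that are significant in the univariate model".
- Its discrimination: "The ability of the multivariate logistic model to correlate with the LAV max group will be verified using receiver operating characteristic (ROC) curves".
- Accuracy measures: "The overall accuracy, sensitivity, specificity, and positive and negative predictive values for the optimal cutoff will be calculated using the Youden index".

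The confounders are not named. Section 2.6 and Table 2 list demographic variables, comorbidities and treatments as data to be recorded, not as model terms. The Youden sentence does not say which test is being cut. No ROC curve is described for an ECG criterion, for a set of ECG criteria without covariates, or for covariates without the ECG.

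The study's question is about the ECG. The Introduction motivates it by the high specificity (85%–90%) and low sensitivity of existing ECG criteria, and its main aim sets P-wave criteria against LA abnormality on TTE. Section 2.7 sizes the study on the rate of Morris index positivity. The Conclusion expects that the study "will help to define ECG criteria for LA and RA abnormality".

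**The concern.** Adjustment for confounders suits an odds ratio, where the aim is the association of a P-wave criterion with LA enlargement given other patient characteristics. Discrimination is a different quantity. The ROC curve of an adjusted model uses the predicted probability from all its terms, so its AUC is what the ECG and the covariates achieve together. Sensitivity and specificity at a cutoff of that probability likewise belong to the whole model, not to a rule that can be read off an ECG.

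Covariates that are causes or correlates of LA enlargement could supply most of the discrimination. The planned AUC could then look respectable while the P wave contributes little, and it would not show what the ECG criteria achieve by themselves. That bears directly on a study meant to define ECG criteria and motivated by their low sensitivity.

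**Working it through.** **The plan's own figures.** The documents give no AUC. The one calculation they contain is the sample size in section 2.7: n = z² p(1 − p)/d² with p = 0.92, d = 0.06, z = 1.96, which gives 78.54, rounded up to 79. It reproduces. It matters here only because the rate it targets is an ECG-only proportion.

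**Inputs for the illustration (all assumed).** An ECG score and a covariate score, each normal with equal variance in the two LAV max groups and independent within group. Let d be the standardised separation between groups.

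**Formulas.**

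- AUC = Φ(d/√2)
- Combined d = √(d_cov² + d_ecg²)
- Sensitivity = specificity at the Youden point = Φ(d/2)

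**Central case.**

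- Covariates: d_cov = 0.8, AUC = Φ(0.566) = 0.714
- ECG: d_ecg = 0.35, AUC = Φ(0.247) = 0.598
- Combined: d = √(0.64 + 0.1225) = 0.873, AUC = Φ(0.617) = 0.732
- ECG increment: 0.732 − 0.714 = 0.018
- Sensitivity = specificity: Φ(0.175) = 0.57 for the ECG alone, Φ(0.437) = 0.67 for the model

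**Range, ECG AUC held at 0.598.**

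| Covariates-only AUC | Model AUC | Increment from ECG |
|---|---|---|
| 0.664 (d = 0.6) | 0.688 | 0.024 |
| 0.714 (d = 0.8) | 0.732 | 0.018 |
| 0.760 (d = 1.0) | 0.773 | 0.013 |

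**Second set of assumed values.** With a covariate AUC of 0.75, the model AUC is 0.75, 0.76 or 0.80 when the ECG alone has AUC 0.50, 0.60 or 0.70. At ECG AUC 0.60, sensitivity = specificity is 0.57 for the ECG alone and 0.69 for the model.

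**Relaxing independence.** With covariate AUC 0.75, ECG AUC 0.60 and a within-group correlation of 0.3 or 0.5, the model AUC is 0.751 or 0.752. The ECG's share is then smaller still.

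The same model AUC can therefore arise from quite different ECG contributions, and the model ROC alone does not tell them apart.

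**The case against.** Several points can be made for the plan, and most of them limit how far the concern goes.

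- A reader might infer that discrimination due to clinical factors will be presented as that of the ECG. The text does not say so. It labels the result as the ability of the model, and the Conclusion mentions neither the model nor the ROC curve. Misattribution is a risk, not a plan.
- A reader might assume that age, hypertension and heart failure are in the model. Table 2 only records them, and the choice of covariates may be fixed in a fuller document that is not shown.
- A reader might infer that the model will predict its own reference standard, because LAmin, LAVpre and LAEF in Table 1 are tied to LA volume and would probably pass a univariate screen. Nothing makes them candidates, and section 2.8 speaks of confounders. This supports a precautionary sentence and no more.
- A worthless ECG criterion carried along by covariates would usually fail the univariate screen, if that screen applies to ECG terms. The case of an ECG AUC of 0.50 is therefore a limiting case, not a forecast.
- The Youden sentence could refer to a continuous ECG measure, and the sample size implies that an ECG-only rate for the Morris index will be estimated.
- The stated main aim is association. The group comparisons, Spearman correlations, univariate models and adjusted coefficients all give ECG-specific information on it.

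All of this stands. None of it supplies an ECG-only ROC curve, and the association measures do not stand in for one. The concern also does not rest on an omission from a condensed article: section 2.8 states which model the ROC curve belongs to.

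**Conclusion.** The concern holds in a limited form. As written, the one ROC analysis belongs to a model adjusted for confounders, and the accuracy measures most naturally belong to it too. If clinical covariates enter, those figures are joint results and do not give the diagnostic performance of the ECG criteria.

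Under assumed independent binormal scores, a covariate AUC of 0.71 and an ECG AUC of 0.60 give a model AUC of about 0.73. Over covariate AUCs of 0.66 to 0.76, the ECG increment is roughly 0.01 to 0.02. These values illustrate the mechanism and do not predict this study's results, since no AUC is documented and the covariates are not named. If no covariate entered, the issue would largely disappear.

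This is an inexpensive improvement to make before analysis. It does not invalidate the association analyses.

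**What to change.** Amend section 2.8 as follows.

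1. For each ECG criterion alone, and for a model containing only ECG criteria, report sensitivity, specificity, PPV and NPV with confidence intervals. Add an ROC curve and AUC where the measure is continuous or ordinal. For a yes/no criterion, sensitivity and specificity suffice.
2. State which test the Youden cutoff applies to.
3. Report the adjusted model separately, as an increment over a covariates-only model: the AUC difference with its confidence interval and the likelihood-ratio test for the ECG terms.
4. As a precaution, state that LA volume measures and variables derived from them are not eligible as covariates when LAV max group is the outcome.

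The cost is some wording and a few extra model runs on data the study already plans to collect. The headline AUC will probably be lower than that of the adjusted model, but it will describe the ECG criteria.

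### The study is sized to estimate the sensitivity of the Morris index to within 6 points, but the analysis section names no such estimate and ties sensitivity to a data-derived Youden cutoff

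*Protocol article*

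**What the plan says.** Section 2.7 (Sample size calculation) of the protocol article supposes that "92% of patients with LA abnormality might have a positive Morris index". It continues: "We estimate that 79 patients with a positive Morris index are required to determine this rate". The margin it sets is 6 percentage points, at 95% confidence. No other quantity is sized.

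The Introduction defines the Morris index numerically: "terminal negativity of P wave in V_1_ < −0.1 mV and duration >0.04 s". The list in section 2.4 headed "ECG parameters for assessment of LA abnormality" has eight entries. The relevant one is the presence of PtfV1, with neither a threshold nor an electrode position, although V1 is recorded in three intercostal spaces.

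Section 2.8 (Statistical analysis) sets up the reference groups: "Based on the volume of LAV max by echocardiography, 2 groups will be established, as follows: increased volume and normal volume". Section 2.5 puts the cut at 34 ml/m². Section 2.8 then plans t, Mann–Whitney and chi-square tests, Spearman and intraclass correlations, a logistic model adjusted for confounders, and ROC curves for that multivariable model. The next sentence reads: "The overall accuracy, sensitivity, specificity, and positive and negative predictive values for the optimal cutoff will be calculated using the Youden index".

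**The concern.** The proportion of patients with left atrial (LA) abnormality who are Morris-positive is a sensitivity, taken at a definition fixed before the data are seen. That is what section 2.7 pays for. The only sensitivity that section 2.8 names is at an optimal cutoff chosen in the data, and the only ROC analysis described there is that of the multivariable model. That is a different quantity, and the planned precision says nothing about it.

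The study could therefore publish the accuracy of a fitted ECG-plus-covariate model while the figure it was sized on appears without an interval, or not at all. The background argument, that established P-wave criteria are specific but insensitive, would then not be tested with planned estimates.

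**Working it through.** **1. Inputs.** From section 2.7: p = 0.92, half-width d = 0.06, 95% confidence (taken as two-sided, z = 1.96), stated n = 79.

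**2. The plan's own figure.** n = z² p(1 − p) / d² = 1.96² × 0.92 × 0.08 / 0.06² = 78.54, rounded up to 79. This matches exactly. A one-sided version gives 55.3, rounded up to 56, and does not match. So 79 is the number for a single proportion at a fixed definition.

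**3. What 79 would deliver.** Suppose all 79 have increased LA volume.
- At 92%, the half-width is 1.96 × √(0.92 × 0.08 / 79) = 5.98 points.
- With 73 of 79 positive (92.4%), the Wilson interval is 84.4% to 96.5% and the exact interval 84.2% to 97.2%.
- If the true sensitivity were lower, precision would be worse: 1.96 × √(0.7 × 0.3 / 79) = 10.1 points at 70%, and 11.0 points at 50%.

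**4. Which 79.** The denominator of the 92% is patients with LA abnormality, but section 2.7 counts 79 Morris-positive patients. Among Morris-positive patients alone, sensitivity cannot be estimated; only the positive predictive value can. The article gives no prevalence of increased LA volume. Total recruitment needed for 79 patients with increased volume is 79 / prevalence:

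| Assumed prevalence | Total patients |
|---|---|
| 20% | 395 |
| 30% | 264 |
| 40% | 198 |
| 50% | 158 |
| 60% | 132 |

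**5. The two sections side by side.**

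| | Section 2.7 | Section 2.8 |
|---|---|---|
| Object | Morris index | Multivariable model (natural reading) |
| Threshold | Fixed in advance | Chosen by Youden index in the data |
| Precision | ±6 points, 95% | None stated |

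If the Youden sentence referred instead to ROC curves of single ECG variables, the cutoff would still be chosen in the data and would not be the Morris definition. The mismatch holds on either reading.

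**6. Does the 6 points carry over?** This was checked by an illustrative simulation of 300 runs per setting. The assumptions, none of them from the article, are 79 patients with and 79 without increased volume, and one true predictor with an area under the curve of about 0.75, plus noise predictors.

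| Noise predictors | Sensitivity, same data | Sensitivity, new data | Youden index, same data | Youden index, new data |
|---|---|---|---|---|
| 0 | 0.69 | 0.65 | 0.42 | 0.35 |
| 4 | 0.71 | 0.66 | 0.44 | 0.33 |
| 9 | 0.71 | 0.63 | 0.46 | 0.30 |

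The standard deviation of the same-data sensitivity was 0.10 to 0.11. The 95% half-width is therefore 1.96 × 0.10 ≈ 0.20 or slightly more, about 20 points rather than 6.

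**The case against.** A reader might infer that the sensitivity of the Morris index is never obtained and that the study can say nothing about it. The documents do not support that. Presence of PtfV1 is categorical, and its chi-square table against the two volume groups holds the raw proportion positive in each. Section 2.7 also declares the rate and its precision to be wanted. What stands is narrower: section 2.8 names no estimate or interval, and a test of association does not deliver a rate with a stated precision.

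A reader might also infer that accuracy is confined to the multivariable model. The Youden sentence does not name the model, and the word *only* appears nowhere in it. The link comes from the sentence before, which holds the only ROC analysis described.

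Nor is diagnostic accuracy the stated main aim. The Introduction and abstract speak of association and correlation, which the planned tests, correlations and regression do address. The case rests on the sample size basis and the background, not on the aim.

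An article condenses, and per-criterion tables may sit in a fuller document. That would answer a complaint of pure omission. Here two stated passages point at different quantities. Finally, some listed parameters (area, the MVP score, the banded lead I voltage) have no single threshold, so a data-derived cutoff is reasonable for them.

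**Conclusion.** The point holds as a mismatch between sections 2.7 and 2.8. The sample size arithmetic is right, but the sized quantity has no matching estimate or interval in the analysis section. The accuracy figures that are planned concern a data-derived cutoff to which the ±6 points does not apply.

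The figure of about 20 points, and the 4 to 8 points of optimism in sensitivity, depend on the assumed simulation settings. They show the direction and rough scale and are not predictions for this study. The ±6 points itself depends on the 79 being patients with increased LA volume and on a true sensitivity near 92%.

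This should be fixed, but it does not invalidate the study: the data needed will be collected anyway, and the association analyses are unaffected.

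**What to change.** - Add to section 2.8 the sensitivity and specificity of the Morris index at the Introduction's definition, with V1 in the fourth intercostal space, against LAmax > 34 ml/m², with 95% confidence intervals (for example Wilson).
- Do the same for the other criteria with a single stated threshold, such as P-wave duration ≥ 120 ms and a biphasic P wave in the inferior leads.
- Label the multivariable model and its Youden-cutoff results as secondary and exploratory.
- State in section 2.7 that the 6-point precision holds only if the 79 are patients with increased LA volume. Otherwise, restate the precision expected.
- Within-patient comparisons by McNemar's test, and of areas under the curve by DeLong's test, are optional.

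The analysis costs a few 2×2 tables from data already planned and a short edit to two sections. If the authors keep the 6-point target, recruitment must continue until 79 patients with increased volume are enrolled. The total then depends on a prevalence that the article does not give.
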